## Abstract

A growing number of parents delay vaccinations or are deciding not to vaccinate their children altogether. This increases the risk of contracting vaccine-preventable diseases and disrupting herd immunity, and also impairs the trust in the capacities of health care systems to protect people. Vaccine hesitancy is related to a range of both psychological and demographic determinants, such as attitudes toward vaccinations, social norms, and trust in science. Our aim is to understand those determinants in parents, because they are a special group in this issue—they act as proxy decision makers for their children, who are unable to decide for themselves. The fact that deciding to vaccinate is a socially forced choice that concerns a child's health makes vaccine-related decisions highly important and involving for parents. This high involvement might lead to parents overemphasizing the potential side effects that they know to be vaccine-related, and by amplifying those, parents are more focused on the potential outcomes of vaccine-related decisions, which can yield specific pattern of the outcome bias. We propose two related studies to investigate factors which promote vaccine hesitancy, protective factors that determine parental vaccination decisions, and outcome bias in parental vaccination intentions. We will explore demographic and psychological factors, and test parental involvement related to vaccine hesitancy using an online battery in a correlation panel design study. The second study is an experimental study, in which we will investigate the moderating role of parents' high involvement in the specific domain of vaccination decision making. We expect that higher involvement among parents, compared to non-parents, will shape the pattern of the proneness to outcome bias. The studies will be conducted across eight countries in Europe and Asia (Finland, Germany, Hong Kong, the Netherlands, Serbia, Slovenia, Spain, and the United Kingdom), rendering findings that will aid with understanding the underlying mechanisms of vaccine hesitancy and paving the way for developing interventions custom-made for parents.

## Introduction

One of the greatest public health challenges today concerns suboptimal vaccine uptake rates. In 2017, measles affected 21,315 people and caused 35 deaths, according to WHO's press release from 19 February 2018. “The surge in measles cases in 2017 included large outbreaks in 15 of the 53 countries in the (European) region. The highest numbers of affected people were reported in Romania (5,562), Italy (5,006), and Ukraine (4,767)” (World Health Organization, 2018). Greece, Germany, Serbia, the United Kingdom, Spain, Bulgaria, and France also experienced large outbreaks (World Health Organization, 2018). This is a result of suboptimal vaccine rates (World Health Organization, 2017a): in many areas, the coverage rates of common vaccines have decreased below 95% that is postulated as the minimum to herd immunity, the effective halting of the spread of measles and other vaccine-preventable diseases.

While some children cannot be vaccinated for medical reasons and in some areas vaccines are not readily available, a growing number of children are not vaccinated or are vaccinated late largely due to their parents' conscious decision (Pearce et al., 2008). The resistance to be vaccinated or to delay vaccinations despite having available vaccinating services, has been dubbed vaccine hesitancy (Luthy et al., 2009; Gowda and Dempsey, 2013; World Health Organization, 2014). Numerous interventions have been introduced to combat vaccine hesitancy, but many are lacking in success (Sadaf et al., 2013; Dubé et al., 2014; Pluviano et al., 2017). To better combat vaccine hesitancy and optimize interventions, factors associated with parents' decisions on vaccination need to be identified and investigated.

As such, vaccine hesitancy is a multi-layered phenomenon, related, amongst others, to various factors of social and psychological kind. Several studies examining various populations and different vaccines have found that vaccine hesitancy is related, amongst other, to prior beliefs about vaccinations (Smailbegovic et al., 2003; Dubé et al., 2014), perceived benefits of vaccines (Myers and Goodwin, 2011), attitudes toward vaccines (Pareek and Pattison, 2000; Mohd Azizi et al., 2017), whether the child has been previously vaccinated (Pareek and Pattison, 2000), previous experiences with vaccinations (Boes et al., 2017), socioeconomic status (Smith et al., 2004), number of children (Gust et al., 2005), and marital status (Smith et al., 2004). Despite the wide range of findings, the results of several systematic reviews suggest that there are still factors to be identified and further explored (Mills et al., 2005; Larson et al., 2014; Cobos et al., 2015).

The studies about vaccine hesitancy have often focused on parents, who are the key propagators of vaccine hesitancy and consumers of anti-vaccine influences, while the children are the key victims. For parents, vaccinating their children could mean that parents have to witness their child's discomfort and have to face potential potential side effects. At the same time, not vaccinating may lead to contracting vaccine-preventable diseases, potential prosecution in certain countries, enrolment refusal in some schools, disrupting herd immunity, etc. Parents may also face social pressure, such as pressure from health-care professionals (Evans et al., 2001), or other kinds of social pressure, e.g., to be experts on vaccination mechanism and therefore reliable and informed decision makers. In the contemporary context, parents are prompted to take an active role in their children's healthcare (Pyke-Grimm et al., 1999), which places heavy burden on the parent (Wagenaar et al., 1988).

This is especially true in the realm of intensive parenting; one of the most dominant parenting styles today (Arendell, 2000; Smyth and Craig, 2017). The term was coined by Hays (1996) to describe parenting style closely linked to the pressure felt by parents, mostly women, because of their responsibility for all childcare related tasks, children's outcomes (intellectual, social, emotional, and health-related), and their need to protect the child from any harm or disease. These needs, although very common for majority of parents, in highly individualistic societies outturn as the less communal worldviews, and research shows that intensive (salutogenic) parenting was an important rationale for refusing vaccines, as salutogenic parents have higher sense of advocacy and feel more capable of taking care for the children without expert intervention or vaccines (Reich, 2014; Ward et al., 2017).

On discussions about vaccinating their children, parents emphasize the purpose and safety of vaccination rather than the procedure itself (Salmon et al., 2005; Miton and Mercier, 2015). This parental decision is often accompanied by limited knowledge (Downs et al., 2008; Zingg and Siegrist, 2012), threatening campaigns (Ruiter et al., 2014; Stronach, 2015), societal norms (de Visser et al., 2011; Oraby et al., 2014), and official consent (Leask et al., 2011). Vaccine-hesitant parents thus differ from non-parents in their perception regarding the dangers of vaccines, risk of side effects, and protective benefits. Similarly, the perceived danger of vaccines is associated with the reluctance to vaccinate (Wilson et al., 2008), and it has been suggested that this can play an important role in parents' actual decision on mandatory childhood vaccination (Sporton and Francis, 2001).

This high-stake parental position regarding vaccinations is further complicated by the characteristics of the decision itself. Decisions, among themselves, differ depending on whom we are deciding for: ourselves or someone else (Zikmund-Fisher et al., 2006). People also use different strategies when deciding about other people compared to deciding about inanimate objects (Goldstein and Weber, 1995). Additionally, the importance of a decision differs according to its domain (see Meta-Decision-Making Model; Payne et al., 1993). Especially in health-related decisions, the importance of the decision skews decision-making processes and related phenomena, such as proneness to risky decisions (Wang, 1996a; Fagley and Miller, 1997; Kühberger, 1998; Hanoch et al., 2006; Markiewicz and Weber, 2013; Gummerum et al., 2014; Zimerman et al., 2014; Damnjanović and Gvozdenović, 2016), susceptibility to cognitive biases (McNeil et al., 1982; Wang, 1996b; Tanner et al., 2008) and effort of strategies (Edwards et al., 2001; Almashat et al., 2008).

Health-related decisions also differ according to the extent of their importance (Thompson, 2007), which affects the level of involvement decision makers put into a decision (Solomon et al., 2006). Different decisions range on a continuum from fairly routine to those that require extensive thought and have a high level of involvement (Solomon et al., 2006). The level of involvement in the same decision can differ between people (Arora and McHorney, 2000). However, some decisions (e.g., health-related decisions) are generally assumed to be important for the great majority of people (Solomon et al., 2006). Parental decision about a child's health is a special and extreme case of health-related decision (Zikmund-Fisher et al., 2006). It is also highly involving in terms of affect and expectation (Wroe et al., 2004). There is evidence suggesting differences, not only between parents and non-parents (Donovan and Jalleh, 2000), but also parents with children of different ages (Henrikson et al., 2017) regarding intentions to vaccinate and seek information on vaccination. Decomposing involvement and its influence on decision-making processes can help with undermining vaccine hesitancy through minimizing cognitive obstacles to reasoning, which stem from high involvement.

Parental decision on child vaccination is a specific case of health-related decision (Zikmund-Fisher et al., 2006) that is highly involving in terms of affect and expectation (Wroe et al., 2004). When discussing vaccination and immunization, the emphasis is on its purposefulness, potential side effects, and efficacy of vaccination (Salmon et al., 2005; Miton and Mercier, 2015). When normative, but also descriptive theory of decision-making is applied, decisions on vaccination can be analyzed using the decision matrix in which states of nature and alternative decisions are crossed to make cells with different outcomes (see Table 1). It can be stipulated that, when deciding on vaccination, people tend to place major weights on the outcomes, that is on the subjective perception of the outcomes. In other words, as well as some other health-related decisions, decisions on vaccination have an inherent feature of a stronger focus toward the outcome (Gellin et al., 2000; Freed et al., 2004, 2010; Gust et al., 2004; Miton and Mercier, 2015). To parents, the important issue while deciding is the outcome of this decision (e.g., well-being and health of their child) (Goldenberg, 2016). Evaluating prior decisions based on their outcomes is a tendency labeled as the outcome bias (Baron and Hershey, 1988). For instance, parents might overemphasize the immediate vaccine side effects, such as rashes or swelling, and use these side effects as justification to avoid vaccinating their child (Callender, 2016). In line with this, parents might judge the quality of the potential decision to vaccinate their child based on the consequences of this decision met previously by them or by the sources they are in contact with. Therefore, this decision is specific due to its explicit orientation toward the outcome (Gellin et al., 2000; Freed et al., 2004, 2010; Gust et al., 2004; Salmon et al., 2005).

**Table 1 T1:** Decision matrix: vaccination case.

		**STATES OF NATURE**		
		**Vaccines are efficient and risk-free**	**Vaccines are efficient and low-risk**	**Vaccines are extremely dangerous**
Decisions	To vaccinate	Status quo	Status quo	High risk
	Not to vaccinate	High risk	High risk	Status quo

Understanding how both psychological and social factors relate to vaccine hesitancy is important for developing effective interventions. Therefore, the aim of the proposed research is to detect factors associated with and affecting the decisions of parents' regarding vaccination. To do that, we will conduct two separate but related studies. In study 1, socio-demographic and psychological variables will be tested for their connection with differences among parents when it comes to making vaccine-related decisions for their children. In study 2, the role of involvement in decisions regarding childhood vaccinations will be explored in more details. Specifically, we will study whether involvement will moderate the susceptibility to outcome bias with an experimental design.

## Study 1—correlates of intention to vaccinate

### Introduction

In study 1, we aim to explore the demographic and psychological factors that influence parents' vaccine hesitancy. As previously stated, vaccine hesitancy is related to a large range of attitudes, most notably to lower rates of compliance, which lead to drops in vaccination rates (Bloom et al., 2014). Our choice of correlates is in line with the framework of vaccine decision factors proposed by Gowda and Dempsey (2013), and it is important to acknowledge their interrelatedness. Since vaccination intention and hesitancy are multi-layered phenomena, chosen measures are narrowed to broadly cover the three following aspects: parent-specific factors (demographics, knowledge etc.), vaccine-specific factors (perceived vaccine safety and efficacy etc.), and external factors (values, norms, policies, requirements etc.).

#### Trust toward authorities

In the abundance of both affirmative and diminishing information on vaccination, the full picture is seldom easily available and individuals have a hard time forming their own opinions on the topic. Thus, argumentation must rely on evidence, which is accepted largely based on trust (Miton and Mercier, 2015). Trust in relevant actors (such as health professionals, pharmaceutical companies, law makers etc.) in the debate as well as general trust in science play an important role in vaccination decisions (Bedford, 2014; Jolley and Douglas, 2014; Camargo and Grant, 2015). However, this can be challenging as research repeatedly shows that some actors and science as a whole receive a low level of public trust (Lewandowsky and Oberauer, 2016). This can be caused due to high informational pluralism, rendering their argumentation on the topic irrelevant to the public.

Feelings of mistrust could also be part of a general feeling of unease about the complexity of modern society that forces us to rely on others to manage some parts of our lives (Hobson-West, 2007). According to Collins (2009), a general mistrust in science and scientists has enabled a paralyzing form of skepticism and scientific populism that denies the role of science and prompts anti-vaccination decisions.

Parents who have a positive view of the government are more likely to support vaccine policies, and perceive them as beneficial rather than restrictive of their personal freedom (Miton and Mercier, 2015; Highland, 2016). We expect parents who find official pro-vaccination authorities trustworthy to be less vaccine hesitant, show a higher intention to vaccinate, and a higher experience of freedom in the decision.

Previous studies have found that people with higher level of distrust toward authorities are more reluctant to rely on official sources of information (Freed et al., 2011). For that reason, we expect the relationship between level of trust and intention to vaccinate to be moderated by the type of sources consulted to make the decision. We expect level of trust toward authorities to predict the proportion of official sources used for the decision.

Finally, some studies have found that belief in conspiracy theories can predict distrust toward authorities (Darwin et al., 2011; Swami et al., 2011). We expect to replicate this result in the case of vaccine related conspiracy theories.

#### Perceived consensus and norms

Many vaccination decisions are influenced by parents' perception of others when making vaccination decisions (Gust et al., 2004; Leask and MacArtney, 2008; Gowda et al., 2012; Gowda and Dempsey, 2013). People in general tend to rely on consensus cues, because consensus, especially combined judgment of multiple experts, typically implies correctness (Van der Linden and Lewandowsky, 2015; Tom, 2017). However, there is a gap between the low level of scientific consensus perceived by the lay-public, and the actual level of consensus regarding the immunization and vaccination. The Gateway Belief Model proposed by Van der Linden et al. (2015) suggests that reducing the difference between people's subjective perception and the actual level of normative agreement among influential referents can lead to small yet important changes in key personal beliefs. Moreover, perceived scientific consensus has been identified as a key determinant in the public's opinion on, in some aspects equivalent, disputable topics (van der Linden et al., 2017). Due to high involvement aspects of vaccine-related decisions, we assume perceived scientific consensus plays a specific role, as it was the strongest predictor of the acceptance of the scientific arguments in other similar social issues (Lewandowsky et al., 2012). We expect parents who perceive stronger scientific consensus on the topic of vaccination to show less vaccine hesitancy and be more likely to vaccinate their children. We will thus test the correlation of perceived consensus, and the perception of risk with the decision on mandatory childhood vaccination (Wilson et al., 2008; Rolfe-Redding et al., 2012). We expect perceived consensus will correlate more strongly with the intention to vaccinate than perceived vaccination risks. Confidence in vaccines and vaccine-related decisions are also influenced by the individual's perception of societal norms and collective values, as well as their metacognitive perceptions about other groups' (e.g., health professionals) beliefs (Kennedy et al., 2011; Gowda and Dempsey, 2013; van der Linden et al., 2017). Numerous findings suggest normative information is rated as more trustworthy, less resilient to dismissal, and more influential than anecdotal cases (Carrico et al., 2011; Kahan et al., 2011; Lewandowsky et al., 2012; Rolfe-Redding et al., 2012), hence making it more likely to influence decision-making processes.

In situations where social norms are ambiguous, appealing to consensus and unity of norms tends to be more effective in persuading parents to vaccinate (Lewandowsky et al., 2012). Based on findings by Kahan et al. (2009) and Kahan (2010), we predict that the correlation between parents' intention to vaccinate (what we call adherence to the norm) and norms will be moderated by the perception of social consensus of given norms.

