### Methods

#### Design, sample, and procedure

Participants will be parents or primary caregivers of children that are of the recommended age to receive vaccinations from their corresponding countries across Europe and Asia (i.e., Finland, Germany, Hong Kong, the Netherlands, Serbia, Slovenia, and Spain). Participants must be (a) over 18 years old, and (b) a parent or care taker of at least one child under the age of 12 years (Salmon et al., 2005; Jones et al., 2012).

The sample size will be a minimum of 222 participants per country, based on a power analysis for an effect size of 0.15, and 20 predictors in a linear multiple regression model. The final sample size will not have a difference greater than 10% between each country. To make sure that there aren't any significant differences between the sample sizes of the different countries, if the sample of any country exceeds 10% of the mean, some participants will be randomly discarded until the criterion is met.

The questionnaire is programmed in JavaScript and will be administered online. To take part in the study, participants will need an electronic device with access to internet. The link with an unbiased invitation letter will be posted on different social media platforms, forums and websites, targeting a wide range of parents from the entire vaccine-hesitancy spectrum. Once the link is opened, participants will first be given a brief introduction of the study. Participants will then read and sign an informed consent, which states they are able to halt and withdraw from the study at any moment without providing a reason, and that they agree for their anonymized data to be analyzed for future publications. Participants will be asked to compose a unique identification code (consisting of their parents' initials, and month of birth), which will be used to identify their data if they decide to withdraw their data after completing the study. After that, participants will be asked to provide their demographic information and complete a battery of vaccination- and decision-making-related questions, with a total of 115 items (the complete battery is in Appendix 1). Participants will be able to leave items unanswered. The study will take ~25 min to complete, but will vary depending on participants' speed of responding. This procedure was ethically approved by the Institutional Review Board of the Faculty of Philosophy at the University of Belgrade.

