##### Vaccination scales

To measure the perceived risk of (not) vaccinating may cause in children and society, we will use the vaccination scale developed by Horne et al. (2015). It is a 5-item scale that measures people's general attitude toward the vaccination (i.e., “Vaccinating healthy children helps to protect others by stopping the spread of diseases,” “I plan to vaccinate my children”). This test has proper psychometric features, including a high internal consistency (α = 0.84), and good predictive validity for past and future vaccination behavior, it has not been used in Europe so far.

Furthermore, the Vaccine Conspiracy Belief scale (Shapiro et al., 2016) will be added at this part. This scale contains 10 items, which examine the belief in the conspiracy theory that different entities try to hide the risk of vaccines. This shows the deception rather than the general attitude people have (Shapiro et al., 2016). An example of this item is: “The government is trying to cover up the link between vaccines and autism.” This scale has a very high level of internal consistency (α = 0.94) and is a good predictor of the willingness of parents to vaccinate their children.

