### Proposed analysis

We will use statistical software (Matlab, R) for data analysis. We will analyse samples from each country separately because the differences in terms of language, legal framework in relation to vaccines, demographical characteristics and representativeness make the comparability between the different samples, and thus, their conjugate analysis, difficult (Ember et al., 1998).

For each sample, a factor analysis will be conducted to reduce the number of factors and control for interrelatedness of the variables. Two clusters of variables will be included: demographics (age, education level, number of children, mean age of children), and vaccine-related decision constructs (scores on scales on vaccination, vaccine hesitancy, perceived freedom of the decision, choice overload, actively open-minded thinking, trust toward authorities, availability of relevant information, perceived scientific consensus on vaccination, subjective estimation of percentage of children vaccinated on the country, perceived social consensus on vaccination, risk taking, and elaboration of potential outcomes). We expect the factor structure of each sample to be similar. With the reduced number of factors, a multivariate linear regression analysis will be conducted and the predictive power will be tested. The aforementioned factors will serve as predictors, and the parental intention to vaccinate (“I plan to vaccinate my child in accordance to the official vaccination schedule of my country”) will serve as criterion. All variables mentioned will also be included in a multivariate analysis of variance to see if there are differences between them depending on the level of adherence (total adherence, not completely total adherence, no adherence at all) to the official vaccination schedule of their children. We will test the proposed model of mediation (Figure 1) using regression analysis and compare it to a more complicated model with involvement as an additional factor.

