### Anticipated results

The samples of this study will consist of data obtained in eight separate countries. This presents both challenges and possibilities. As some of the factors underlying vaccine hesitancy are context-specific and vary across time and place (Dubé et al., 2014), research in multiple countries is needed to understand vaccine hesitancy more fully on a local level. By analyzing our samples separately, we expect the study to contribute to knowledge on locally relevant factors related to vaccine hesitancy. However, the samples are unlikely to be representative in their respective countries, which limits the reliability of out conclusions on local, but not so much on the general level. Special care will also be taken to make sure that we sample people from all parts of the vaccine-hesitancy spectrum; the call for participants will be posted in different interest groups online along with general population call.

Given the sensitive nature of the topic, it is possible for the participants who participate in the study to have stronger convictions toward vaccines in one way or another, which might further decrease the representativeness of the vaccine hesitancy continuum—we want to include parents with various degrees of their hesitancy and strength of their convictions in order to avoid bipolarization. To decrease the effect of the topic on the motivation to participate, all the communication (e.g., invites, instructions) will be neutral in terms of referencing to potential harms and benefits of vaccination as well as any moral judgements of the decision.

Due to the wide range of phenomena of the present study, we hypothesize to find the following factors to reinforce the intent to vaccinate one's child: trust toward authorities, perceived social and scientific consensus, availability of relevant information, along with previously identified demographic characteristics and open-minded thinking. At the same time, we expect to confirm that vaccine hesitancy, perceived freedom, choice overload, the use of informal sources and susceptibility outcome bias serve as reinforces of delaying or omitting mandatory childhood vaccination. All our hypothesized connections can be seen in Figure 1.

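### Study 1 expects perceived consensus to correlate more strongly with intention than perceived risk, but names only tests of the separate correlations and no test of their difference

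*Protocol article*

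**What the plan says.** The Study 1 section on perceived consensus and norms first announces the test: "We will thus test the correlation of perceived consensus, and the perception of risk with the decision on mandatory childhood vaccination". The comparative expectation follows directly: "We expect perceived consensus will correlate more strongly with the intention to vaccinate than perceived vaccination risks".

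The Study 1 proposed analysis says "We will analyse samples from each country separately". It lists a factor analysis and then a regression on the resulting factors: "With the reduced number of factors, a multivariate linear regression analysis will be conducted and the predictive power will be tested". It adds a multivariate analysis of variance by adherence, a mediation model, a qualitative analysis and several ANOVAs. None of these compares the two correlations, or two regression coefficients.

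On size, the methods section states "The sample size will be a minimum of 222 participants per country". It derives this number from a regression with 20 predictors and an effect size of 0.15. That section lists seven countries, while the anticipated results say "The samples of this study will consist of data obtained in eight separate countries".

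Perceived risk is assigned to a five-item vaccination scale whose two example items are "Vaccinating healthy children helps to protect others by stopping the spread of diseases,” “I plan to vaccinate my children". Perceived consensus is measured with additional Likert-type items, for which no reliability is given. The outcome is a single Likert-type intention item.

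**The concern.** The expectation is about a difference between two dependent correlations that share one variable, intention. Testing each correlation has the null value zero and answers a different question. Both can be significant and equally strong. One can be significant and the other not while the two barely differ.

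The regression does not fill the gap. Both constructs enter the same factor analysis and may load on one factor, and then no separate coefficients exist to compare.

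What is at stake is a ranking of determinants. The article presents its findings as groundwork for interventions aimed at parents, and a statement that consensus outweighs perceived risk bears on what such messages stress. Under the plan as written, that statement would rest on inspection of two sample values, with no error control.

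**Working it through.** **Inputs.** From the article: 222 per country, effect size 0.15, 20 predictors, countries analysed separately, seven or eight countries. Assumed, because the article does not give them: true correlations of 0.1 to 0.5 (both measures scored so that higher goes with more intention), correlation between the two measures of 0 to 0.5, normal data, two-sided 0.05 for each correlation.

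**1. The plan's own figure.** Read 0.15 as Cohen's f². For the overall F test the noncentrality is λ = f² × N = 0.15 × 222 = 33.3, with 20 and 222 − 21 = 201 degrees of freedom. At α = 0.05 the power is 0.951, and 222 is the smallest N that reaches 0.95. The figure reproduces exactly, with α and power inferred. It sizes the regression, not this comparison.

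**2. Rule A: the larger absolute sample correlation counts as support.** With equal true correlations the two are exchangeable, so the rate is 1/2. Simulation at N = 222 (20,000 samples per setting) gave 49.5-50.6%. If consensus must also be significant, the rate is 23-27% at 0.1 and 47-50% at 0.2 or more.

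**3. Rule B: consensus significant, risk not.** The critical correlation is t/√(N − 2 + t²) = 1.971/√(220 + 3.88) = 0.132. Fisher's z gives the chance p that one correlation is significant: p ≈ Φ[(atanh ρ − atanh 0.132) × √219]. With roughly independent sample correlations the rule fires at p(1 − p).

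| True ρ (both) | p | p(1 − p) | Simulated, intercorrelation 0 to 0.5 |
|---|---|---|---|
| 0.1 | 0.32 | 0.22 | 15-22% |
| 0.2 | 0.85 | 0.13 | 10-13% |
| 0.3 | 0.996 | 0.004 | 0.4% |
| 0.5 | about 1 | about 0 | 0% |

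At 0.3 and above both correlations are almost always significant. The two tests then say nothing about which is stronger, and only the unprotected ranking is left.

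**4. A test of the difference.** Let a and b be the correlations of consensus and risk with intention, c the correlation between the two measures, D = 1 − a² − b² − c² + 2abc, and m = (a + b)/2. Williams' statistic is

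t = (a − b) × √{(N − 1)(1 + c) / [2D(N − 1)/(N − 3) + m²(1 − c)³]}, with N − 3 degrees of freedom.

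With equal true correlations its simulated rate of favouring consensus was 4.8-5.3% one-sided at 0.05, and 2.3-2.7% two-sided at 0.05 in the predicted direction.

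**5. Power of that test at 222, c = 0.3 assumed.** For 0.50 against 0.40: D = 0.62, m² = 0.2025, so the expected t is about 0.10 × √(287.3/1.321) = 1.475. Power is about 1 − Φ(1.971 − 1.475) = 0.31 (simulated 32%). For 0.40 against 0.30: D = 0.732, expected t about 1.375, power about 0.28 (simulated 28%). For 0.50 against 0.30: D = 0.66, expected t about 2.88, power about 0.82 (simulated 82%).

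**6. Across countries.** Even a valid test, if any one country counts as support, errs with probability 1 − 0.975⁷ = 16% for seven countries or 1 − 0.975⁸ = 18% for eight (independent samples).

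**The case against.** The strongest defence is that this is an omission, not an error. The article is condensed, the analysis plan is not shown, and the choice of test for two dependent correlations is often left to it. The sentence announcing the test comes before the comparative one and may refer back to the simpler expectation that stronger perceived consensus goes with less hesitancy. Testing each correlation suits that expectation. On this reading the comparison has no stated method rather than a wrong one. That is a fair reading, but it leaves the comparative claim without support: the article names a test in the adjoining sentence, lists its analyses at some length, and none of them addresses the difference.

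Three objections on size stand in full.

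- A reader might infer that the expectation will be confirmed in about half of the countries when the two relations are equal. The documents do not support this, because they never say that the larger correlation wins.
- A reader might infer that support in at least one country is nearly certain (1 − 0.5⁷ = 99.2%, or 1 − 0.5⁸ = 99.6%). This needs the same unstated rule, and also that any single country counts as overall support. The article says only that separate analysis serves locally relevant knowledge.
- A reader might fear that a negatively scored risk measure would win or lose on sign alone. The wording concerns strength, and both example items of the risk scale are pro-vaccine, so agreement should go with more intention.

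Equal measured correlations are also a doubtful reference point. One risk-scale item nearly restates the outcome, which would tend to raise the risk correlation and work against the authors' expectation. A formal test on the full scale would therefore test a contaminated contrast, and the fix has to deal with this.

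**Conclusion.** The point holds in limited form. The article states a comparative hypothesis, the test it names addresses the separate correlations, and nothing in the Study 1 analysis section contrasts them. The plan as written gives no valid basis for saying that one relation is stronger.

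The size is conditional on a decision rule that the article does not state. With equal true correlations and 222 per country, support would arise about 50% of the time per country under Rule A. Under Rule B the rate runs from 15-22% at a correlation of 0.1 down to practically zero at 0.3 or more. These figures rest on the assumed correlations and on normal data. They show what could happen under plausible readings, not what the study will do. This is one expectation in a correlational survey, but the repair is cheap and uses data already to be collected.

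**What to change.** Add a short statement to the Study 1 proposed analysis:

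1. Score both measures so that a higher value predicts more intention.
2. For this comparison, leave the item on planning to vaccinate one's children out of the risk score, because it nearly restates the outcome.
3. In each country report the difference between the two correlations with a 95% confidence interval, by the Williams or Steiger method for dependent correlations or by bootstrap. The bootstrap does not rely on normality, which suits a single Likert-type outcome.
4. Claim a stronger relation for consensus only where the interval excludes zero in that direction. Otherwise report both correlations without ranking them.
5. Read the country results together, not as support from any single country.
6. State that an interval including zero does not show equality, given the low power for a difference of 0.10.

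The cost is a few sentences and one extra analysis per country, with no new data. The risk score for this comparison would have four items instead of five, so its published reliability would no longer apply directly. The stronger relation will also be claimed less often.
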